## 4.5 Exposure to the intervention

The intervention will be summarised in terms of number of visits, type of visit (face-to-face, online or telephonic or other), if session was in group or individually, and other relevant details.

Given the complexity of the intervention and the fact that it only applies to participants randomised to the intervention group, compliance will be defined and summarised after we have analysed the details of the intervention.

To assess the potential effect of compliance, we will consider performing a complier average causal effect (CACE) analysis using both a propensity-weighted approach and a joint modelling approach [2].

## 4.6 Concomitant Medications

Categories of medications (e.g. blood pressure lowering, nutritional supplements) will be defined during the blind review. The number and proportion of patients taking a medication from each category at least once during the study will be reported. Differences in proportions between groups will be tested using Fisher's exact test.

## 4.7 Diet and physical activity questionnaires

Descriptive statistics will be presented for all diet and physical activity variables described in Sections 3.7 and 3.8 by visit and randomized group.

In addition longitudinal mean plots and repeated-measure generalised linear mixed models will be used to assess differences between groups over time as described in Sections 4.10.1 and 4.10.2.

More detailed analyses will be considered in secondary papers and are not described in this SAP.

## 4.8 Healthcare utilisation

The number of events as well as the number and proportion of participants accessing each service (e.g. hospital, pharmacy, etc.) at least once during the study will be reported overall and by treatment group. Differences in proportions will be tested using Fisher's exact test.

More detailed analyses of healthcare utilisation including costs will be conducted later and are not described in this SAP.

## 4.9 Analysis of the primary outcome

The primary outcome is a change of glycaemic category, at or prior to final visit defined as:

- A change from Normal glucose tolerance (NGT) to impaired fasting glucose (IFG) or impaired glucose tolerance (IGT), or T2DM
- A change from IFG or IGT to T2DM

This will be diagnosed using ADA criteria as given below:

- Normal glucose tolerance (<100 mg/dL fasting and <140 mg/dL post-glucose load)
- Impaired glucose tolerance (<100 mg/dL fasting and 140-199 mg/dL post-load)
- Impaired fasting glucose (100-125 mg/dL fasting and <140mg/dL post-load)
- Type 2 diabetes ( $\geq 126$  mg/dL fasting or  $\geq 200$  mg/dL post-load)

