**Scenario 2: OGTT at <24 weeks of gestation (scenario of second preference)**

[figure not shown]

**Scenario 3: FPG at <24 weeks of gestation (least favoured scenario)**[figure not shown]

These individuals will receive standard GDM care, but will also be exposed to an additional brief standardised educational program to improve knowledge of nutrition and physical activity both during and after pregnancy. The study will also be discussed, as establishing rapport with the participants at this stage will be important to maximise participation in post-pregnancy screening. Further contact will be made with potential participants on at least one occasion after hospital discharge, and prior to 3 months post-childbirth, when women will be invited for an OGTT to determine trial eligibility. Those diagnosed with T2DM using ADA criteria at this time will be referred for appropriate care; all other women will be eligible for trial participation.

The *inclusion* criterion, therefore, is the absence of T2DM (i.e. confirmation of NGT, IFG, or IGT) at 3 to 18 months post-partum OGTT. Consistent with design features of a pragmatic trial [29], *exclusion* criteria will be limited to:

- Confirmed case of Type 2 Diabetes

- Travel time to hospital more than 2 hours (unless individual circumstances will not impede hospital attendance for study visits)
- Lack of access to a mobile telephone
- Use of steroids during pregnancy other than for lung maturation of the baby
- Likelihood of moving residence in the next 3 years

All reasons for exclusion or consent refusal will be carefully recorded.

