### 4.9.2 Survival analysis

Change in glycaemic category for primary outcome as defined in section 2.4.1 will be analysed as a time to event calculated as the number of days between randomisation and the day of the event. For subjects with no event, data will be censored on the day of the last OGTT test results.

Survival by treatment arm will be described using a Kaplan-Meier plot with 95% confidence interval will be reported by treatment arm. If available, median time to event as well as quartiles will be derived from the Kaplan-Meier estimates. Censoring will be done at time of last OGTT test.

A Cox model will be used to estimate the Hazard ratio of the two arms (Intervention compared to Control). The Cox model will include the randomised group as well as prior use of insulin as fixed effects and study site as a random effect [4]. We will visually assess the proportional hazard assumption. SAS Proc PHREG will be used.

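### The OGTT category limits in SAP 4.9 and protocol 3.4 leave combined IFG+IGT unclassified, contradicting the SAP's own tables and figures, which count it as prediabetes

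*Combined protocol and SAP*

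**What the plan says.** SAP 4.9 states the primary event as two transitions: "A change from Normal glucose tolerance (NGT) to impaired fasting glucose (IFG) or impaired glucose tolerance (IGT), or T2DM" and "A change from IFG or IGT to T2DM". SAP 2.4.1 lists the same transitions and refers to 4.9 for the detail. SAP 4.9.2 ties the primary Cox analysis to that list: "Change in glycaemic category for primary outcome as defined in section 2.4.1 will be analysed as a time to event".

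Four sets of limits follow in SAP 4.9, and protocol 3.4 has the same four:

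- NGT: "Normal glucose tolerance (<100 mg/dL fasting and <140 mg/dL post-glucose load")
- IGT: "Impaired glucose tolerance (<100 mg/dL fasting and 140-199 mg/dL post-load")
- IFG: "Impaired fasting glucose (100-125 mg/dL fasting and <140mg/dL post-load")
- T2DM: fasting at least 126 mg/dL, or post-load at least 200 mg/dL.

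Other parts of the SAP recognise a further group:

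- SAP 4.9.1 lists IFG + IGT as its own descriptive category, separate from unknown status.
- Table 7 gives it a row beside IFG alone and IGT alone, directly after the pre-diabetes row.
- The note to Figure 3 splits pre-diabetes into three parts, and the combined state is the third.
- The title of Figure 4, the survival plot for this endpoint, describes moving from normal into prediabetes or T2DM, or from prediabetes into T2DM.
- SAP 4.9.4 and 4.9.5 use prediabetes as a baseline covariate and subgroup, without OGTT limits.

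**The concern.** IFG requires a 2-hour value below 140 and IGT requires a fasting value below 100, so a woman with both values in the intermediate range satisfies neither. A derivation coded from SAP 4.9 would score a change from normal to 110/120 mg/dL (fasting/2-hour) as an event and a change to 110/160 as none, although the second is the larger deterioration. It would also have no start category for a woman who enters at 110/160 and later meets the T2DM limits.

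What is at stake is the primary event count. One programmer could follow 2.4.1 and 4.9, another could follow Figures 3 and 4, and each would be faithful to the SAP while obtaining different counts. The HbA1c/FBG sensitivity analysis in SAP 4.9.6 does not repair this, because it sends every visit with an OGTT back to the 4.9 definitions. Only at visits without an OGTT does it make pre-diabetes the residual category, which leaves no gap.

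**Working it through.** **1. Coverage of the four definitions (SAP 4.9, protocol 3.4).**

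| Fasting, mg/dL | 2-hour <140 | 2-hour 140-199 | 2-hour ≥200 |
|---|---|---|---|
| <100 | NGT | IGT | T2DM |
| 100-125 | IFG | **none** | T2DM |
| ≥126 | T2DM | T2DM | T2DM |

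Every integer pair with fasting 60-199 and 2-hour 60-299 mg/dL was classified. Exactly one block is left out: 26 fasting values × 60 post-load values = 1,560 pairs. No pair falls in two categories. The gap concerns only women with both values in the intermediate range; a value at or above either T2DM limit is classified.

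**2. Consequence for the event, by source.**

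| Transition | SAP 2.4.1 with 4.9, literally | Figure 4 title with Figure 3 note |
|---|---|---|
| NGT to 110/120 | event | event |
| NGT to 110/160 | no listed transition | event |
| Baseline 110/160 to T2DM | no qualifying start category | event |

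**3. After the fix.** Adding fasting 100-125 with 2-hour 140-199 as a third form of prediabetes gives every pair exactly one category. The planned sample size does not change, because the 20% control incidence is assumed directly and not built up from the categories.

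**4. The plan's sample size (SAP 2.6).** Inputs are control risk 0.20, relative risk 0.65 (so 0.20 × 0.65 = 0.13), two-sided 0.05, 90% power, a chi-square test and 20% missing outcomes. SAP 2.2 gives 1:1 allocation. With p̄ = 0.165,

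n per arm = [1.960√(2p̄(1−p̄)) + 1.282√(p1(1−p1) + p2(1−p2))]² / (p1−p2)² = 589, or 1,178 in total.

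1,178 × 1.2 = 1,414, which reproduces the stated number. With 20% missing, 1,414 × 0.8 / 2 = 565.6 per arm are evaluable, and

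z = [(p1−p2)√n − 1.960√(2p̄(1−p̄))] / √(p1(1−p1) + p2(1−p2)) = (1.665 − 1.029) / 0.523 = 1.217, which gives power 88.8%.

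The shortfall from 90% comes from multiplying by 1.2 where division by 0.8 would give 1,473. That is a separate matter; 88.8% is only the starting point here.

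**5. Size under an assumed share.** The documents do not say what share of events involves the combined state. If a share s is lost equally in both arms, both risks are multiplied by (1 − s):

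| s (assumed) | Control risk | Intervention risk | Power |
|---|---|---|---|
| 0 | 0.200 | 0.130 | 88.8% |
| 5% | 0.190 | 0.1235 | 86.9% |
| 10% | 0.180 | 0.117 | 84.7% |
| 20% | 0.160 | 0.104 | 79.5% |

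The relative risk stays at 0.65 in every row, so this calculation shows a loss of precision and no bias.

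**The case against.** The strongest reply is that the SAP already shows what is meant. Figure 3 makes IFG + IGT part of pre-diabetes, and Figure 4 words the event in terms of prediabetes. Table 7 and Figure 3 cannot be produced without deriving the combined state. SAP 3.12 requires double programming or code review of key analyses, with discrepancies settled by a third statistician without access to the impacted results. Protocol 2.1 likewise groups women with IGT and/or IFG into one 40% category, which with 28% NGT and 32% T2DM makes 100%. All of this stands as evidence of intent, and a literal miscoding would probably be caught. It does not amend 2.4.1 or 4.9, and a figure title should not have to override the primary endpoint definition.

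The reply is also right on size. The share is assumed. Protocol 5.1.4 continues follow-up for women who change category without T2DM, so even on the literal reading a woman who starts with NGT and shows the combined state at one OGTT would be counted if a later OGTT shows isolated IFG, isolated IGT or T2DM. For such women the event is delayed and not lost, so the table overstates the loss for any given share.

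A reader might also infer from the eligibility wording in protocol 3.2 ("i.e. confirmation of NGT, IFG, or IGT") that women with combined IFG+IGT could not enter. The same section refers those with T2DM for care and makes all other women eligible, so eligibility is not affected.

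**Conclusion.** The definition is wrong as written: followed literally, SAP 2.4.1, 4.9 and 4.9.2 fail to count two kinds of deterioration that the SAP's own figures count. It is an internal contradiction with a clear intended reading.

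Two stronger readings are tempting and are not supported. One is that the trial will drop these events; Table 7 and Figures 3 and 4 point the other way. The other is that the hazard ratio is biased to the null. That would require the intervention to prevent mainly the larger deteriorations, and nothing in the documents supports that premise.

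The gap itself is certain and its size is not. If 5-20% of events were uncounted equally in both arms, power would be 86.9% to 79.5% against 88.8%. This range rests on the SAP 2.6 inputs, the chi-square approximation used there for planning, an assumed share, and permanent loss of every affected event. It is an upper bound on the loss for each share.

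**What to change.** Bring SAP 2.4.1 and 4.9 and protocol 3.4 into line with the Figure 3 note and the Figure 4 title:

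- Define endpoint prediabetes as fasting 100-125 mg/dL and/or 2-hour 140-199 mg/dL, with neither T2DM limit met. It comprises IFG only, IGT only and both.
- State the event as NGT to prediabetes or T2DM, or prediabetes to T2DM.
- Use the same derivation for baseline glycaemic status, the covariate in SAP 4.9.4, the subgroups in SAP 4.9.5 and 4.10, and the OGTT visits in SAP 4.9.6.

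The cost is about one sentence in each document and one line of derivation code, with no new data and no change to the sample size. The change belongs before database lock and unblinding, where SAP 2.1 places finalisation of the plan. If it is made later, record it as a clarification and cite the existing table and figure text as the basis, so that it is not taken for a data-driven choice.

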### 4.9.1 Descriptive analyses

The number and proportion of subjects in each glycaemic category will be reported by group and by visit according to the six following categories:

- 1) Normoglycaemia
- 2) IFG
- 3) IGT
- 4) IFG + IGT
- 5) T2DM
- 6) Unknown glycaemic status

This will be done both using a table and a stacked bar chart.

### 4.9.2 Survival analysis

Change in glycaemic category for primary outcome as defined in section 2.4.1 will be analysed as a time to event calculated as the number of days between randomisation and the day of the event. For subjects with no event, data will be censored on the day of the last OGTT test results.

Survival by treatment arm will be described using a Kaplan-Meier plot with 95% confidence interval will be reported by treatment arm. If available, median time to event as well as quartiles will be derived from the Kaplan-Meier estimates. Censoring will be done at time of last OGTT test.

A Cox model will be used to estimate the Hazard ratio of the two arms (Intervention compared to Control). The Cox model will include the randomised group as well as prior use of insulin as fixed effects and study site as a random effect [4]. We will visually assess the proportional hazard assumption. SAS Proc PHREG will be used.

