## 2.5 Randomisation and blinding

Randomisation occurred through a central, computer-based randomisation service, and was stratified by country, centre and use of insulin during pregnancy. By necessity, neither site investigators nor participants was blinded to allocation (intervention vs. usual care). However, all central study staff, statisticians, and outcome adjudicators were and will remain blinded until final database lock.

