## 2.6 Sample Size

A sample size of 1414 women with GDM will provide 90% power ( $2\alpha=0.05$ ) to detect a relative risk of 0.65, assuming that the control group cumulative incidence for change in glycaemic category will be 20% at 24 months and allowing for 20% of missing outcome data.

The initial power calculation was based on a chi-square test comparing two proportions at 24 months; however, to account for various study durations, the primary analysis will consist in a survival analysis of time to change in glycaemic category which is expected to have at least the same power as a comparison of proportions.

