### 4.1 General Principles

Analyses will be performed using SAS Enterprise Guide version 8.3 or higher (SAS Institute Inc., Cary, NC, USA).

All variables will be analysed by descriptive statistical methods. The number of data available and missing data, mean, standard deviation, minimum, quartiles, median, and maximum will be calculated for continuous data. Frequency tables will be generated for categorical data. For categorical variables, the number and percentage of patients with a specific level of the variable will be presented.

All tests will be two-sided with a type-I error rate of 5%. Analyses of the primary outcome (change in category of glycaemia from normoglycaemia to IGT, IFG or T2DM or from IFG or IGT to T2DM) will be unadjusted for multiplicity; however, we will control the family-wise error rate across secondary outcomes using a Holm-Bonferroni correction [2]. No other multiplicity adjustment will be applied.

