#### **4.9.4 Adjusted analyses**

Both the Cox and Poisson models will be repeated after adding the following covariates to the model: prediabetes (yes/on), BMI (underweight, normal, overweight, obese), time since GDM-affected pregnancy (as a continuous variable, measured in months) and age (as a continuous variable, measured in years).

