| Time Since Delivery
N
mean (SD)
Q1 Q2 Q3
Min, Max     |  |  |  |
| Family History of Diabetes
Yes
No                           |  |  |  |
| Family History of Hypertension
Yes
No                       |  |  |  |
| Past History of Gestational Diabetes
Yes
No                 |  |  |  |
| Use of Insulin in Index Pregnancy
Yes
No                    |  |  |  |
| Past Use of Insulin
Yes
No                                  |  |  |  |
| Past Use of Medication
Yes
No                               |  |  |  |
| Alcohol Consumption
Yes
No                                  |  |  |  |
| Tobacco Use
Yes
No                                          |  |  |  |
| Height
N                                                       |  |  |  |

|                                                                                                              |  |  |  |
|--------------------------------------------------------------------------------------------------------------|--|--|--|
| mean (SD)
Q1 Q2 Q3
Min, Max                                                                            |  |  |  |
| Weight
N
mean (SD)
Q1 Q2 Q3
Min, Max                                                      |  |  |  |
| BMI
Underweight
Normal
Overweight
Obese                                                   |  |  |  |
| HbA1c (%)
N
mean (SD)
Q1 Q2 Q3
Min, Max                                                   |  |  |  |
| Glucose 0 min (mmol/L) at
baseline postpartum (mg/dl)
N
mean (SD)
Q1 Q2 Q3
Min, Max   |  |  |  |
| Glucose 120 min (mmol/L) at
baseline postpartum (mg/dl)
N
mean (SD)
Q1 Q2 Q3
Min, Max |  |  |  |
| Waist Circumference
N
mean (SD)
Q1 Q2 Q3
Min, Max                                         |  |  |  |
| WC(>80cm)
Yes
No                                                                             |  |  |  |
| Hip Circumference
N
mean (SD)
Q1 Q2 Q3
Min, Max                                           |  |  |  |
| Waist/Hip Ratio
N
mean (SD)
Q1 Q2 Q3
Min, Max                                             |  |  |  |
| Hypertension
Yes
No                                                                             |  |  |  |

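### Free improvement: stratify the primary Cox model by baseline glycaemic status, which decides what counts as an event; the likely gain is about 1 to 3 points of power

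*Combined protocol and SAP*

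**What the plan says.** SAP 4.9 makes the event depend on where a woman starts. A woman with NGT has an event on reaching IFG, IGT or T2DM; a woman with IFG or IGT has one only on reaching T2DM.

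The primary model is in SAP 4.9.2: "The Cox model will include the randomised group as well as prior use of insulin as fixed effects", plus a random site effect. A footnote to SAP Table 8 marks this survival analysis as primary. Baseline status comes in only afterwards. SAP 4.9.4 says: "Both the Cox and Poisson models will be repeated after adding the following covariates to the model: prediabetes (yes/on" and goes on to BMI, time since the index pregnancy and age. SAP 4.9.5 fits baseline status with its interaction with arm, as a subgroup analysis.

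SAP 2.5 says that randomisation "was stratified by country, centre and use of insulin during pregnancy". Glycaemic status is not among the factors.

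The insulin term has several names. SAP 4.9.2 and 4.9.3 refer to prior use. Protocol 3.1 and SAP 4.9.5 refer to the index pregnancy, and SAP 2.5 and 4.10.2 to use during pregnancy. SAP Table 3 has one row for insulin in the index pregnancy and a separate row, "Past Use of Insulin".

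**The concern.** The two baseline groups are followed to different endpoints, so there is no reason to expect them to share a hazard. The primary model nevertheless gives them one baseline hazard within site and insulin level. Neither the randomisation nor the primary model controls a factor that is built into the outcome definition. The SAP is also uneven here: 4.10.2 adjusts every continuous secondary outcome for its baseline value, while the primary outcome is not adjusted for its own starting category.

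What is at stake is efficiency, and protection of the primary estimate against a chance difference between arms in the share of prediabetic women. Separately, a programmer reading 4.9.2 could choose the wrong one of two insulin variables for the primary model.

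**Working it through.** **1. The plan's own figure.** SAP 2.6: "A sample size of 1414 women with GDM will provide 90% power" "to detect a relative risk of 0.65", with a "control group cumulative incidence for change in glycaemic category will be 20% at 24 months", two-sided 5% and 20% missing outcomes. For 20% versus 13%, the pooled chi-square formula is

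n per arm = [1.96·√(2·0.165·0.835) + 1.2816·√(0.20·0.80 + 0.13·0.87)]² / 0.07² = 588.8, so 589.

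589 × 1.20 = 707 per arm, which is 1414 in total and matches the plan. With 20% missing, 1414 × 0.80 = 1131 women remain and power is 88.8%. (Dividing by 0.80 instead would give 737 per arm, 1474 in total.) No covariates enter this calculation.

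**2. Inputs for the comparison.**
- Hazard ratio implied by the design: ln(0.87)/ln(0.80) = 0.624, applied within each baseline group.
- Prediabetic share: not given for the trial. The pilot in protocol 2.1 had 28% NGT and 40% IFG/IGT once T2DM is set aside, so 40/68 = 59%. This is an assumption.
- Ratio g of the hazards in the two baseline groups: not given, so a range is used in both directions.

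**3. Method.** Take 24 months as the time unit and constant hazards, with h the hazard in the NGT group. Choose h so that control risk is 0.41·[1 − exp(−h)] + 0.59·[1 − exp(−g·h)] = 0.20 (for NGT higher, replace g by 1/g). With 1131 women censored at 24 months, find the limit and the information of the Cox log hazard ratio, unstratified and stratified. Power = Φ(|log HR|·√information − 1.96).

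| Ratio between baseline groups | IFG/IGT higher: unstratified HR | Gain (points) | NGT higher: unstratified HR | Gain (points) |
|---|---|---|---|---|
| 1 | 0.624 | 0 | 0.624 | 0 |
| 2.5 | 0.628 | 0.9 | 0.630 | 1.2 |
| 3 | 0.630 | 1.2 | 0.632 | 1.7 |
| 4 | 0.632 | 1.7 | 0.636 | 2.6 |
| 5 | 0.634 | 2.1 | 0.639 | 3.4 |
| 8 | 0.637 | 2.9 | 0.647 | 5.3 |

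Stratified power is about 88% to 89% in every row.

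**4. Which ratio is credible?** Protocol 2.1 cites 15.2 T2DM cases per 100 person-years in prediabetic women with prior GDM. Over 24 months that is 1 − exp(−0.304) = 26.2%. Keeping 20% overall, the NGT risk is (0.20 − 0.59 × 0.262)/0.41 = 11.1%, and the ratio is 0.304/0.117 = 2.6. Simulation with follow-up uniform over 12 to 36 months gives 87.5% unstratified and 88.3% stratified, a gain of about 1 point.

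A gain of about 5 points needs something like 40% in NGT and 6.1% in prediabetes: ln(0.60)/ln(0.939) = 8.1-fold. Simulated power is then 83.7% versus 89.2%. But 6.1% is about a quarter of the 26% above.

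**5. Sensitivity to the share.** With within-group HR 0.65 and only 30% prediabetic women, who have the higher hazard, a 5-fold ratio already costs 5.0 points.

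**6. Chance imbalance.** The standard deviation of the between-arm difference in prediabetic share is √(0.59·0.41·4/1131) = 2.9 percentage points. A 2-SD difference (5.8 points) shifts arm-level event risk by 0.058 × (26.2 − 11.1) = 0.9 points on a base of 20%. With risks of 35% and 9.6% it is 0.058 × 25.4 = 1.5 points.

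**The case against.** The strongest reply is that nothing is broken. A primary model built on the randomisation factors, with prognostic covariates in a supporting model, is a defensible pre-specified choice. The planned effect, 20% versus 13%, is itself marginal. If those marginal risks are held, unstratified power stays at about 88% to 89% whatever the ratio, so the omission does not take the trial below plan. With IFG/IGT as the higher-hazard group, stratifying then adds 0.5, 1.1, 1.6 and 1.9 points for ratios of 2, 3, 4 and 5. The adjusted hazard ratio is printed under the primary one in Table 8, and 4.9.5 will show any difference by status. All of this stands.

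It does not remove the point. The models in 4.9.4 and 4.9.5 are secondary, and 4.9.4 brings in four covariates together, so neither improves the primary test or estimate.

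A reader might infer more: that the hazard ratio is biased towards 1, that proportional hazards fails, or that some 5 points of power are lost. The documents do not support these readings. The shift in the hazard ratio is the gap between a marginal and a within-group quantity; it is about 0.01 at ratios of 2.5 to 4 and zero when rates are equal. Any departure from proportional hazards from this source is mild, and 4.9.2 already includes a visual check. The 5-point figure rests on event rates that the documents do not give and that their one rate for prediabetic women with prior GDM argues against.

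**Conclusion.** The point holds as a free improvement, not as an error that threatens the result. The unadjusted test is valid. With a 59% prediabetic share, stratifying is worth about 1 to 3 points of power for hazard ratios of about 2.5 to 4 between the baseline groups. It is worth about 5 points only near 8-fold with NGT the higher-hazard group, and nothing when rates are equal. It also removes chance imbalance in baseline status from the primary estimate.

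These sizes rest on the pilot mix, constant hazards, 20% control risk and a common within-group hazard ratio of 0.624. The documents give neither the trial's baseline mix nor event rates by status, and do not settle which group has the higher rate. The insulin wording is a minor naming point that depends on none of these assumptions; 4.9.5 and 4.10.2 suggest that the randomisation stratum was meant.

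**What to change.** Before database lock and unblinding:

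- **SAP 4.9.2:** stratify the primary Cox model by baseline glycaemic status, NGT versus IFG/IGT (including women with both). State that the hazard ratio is then a within-status effect.
- **SAP 4.9.3:** add the same variable as a fixed effect in the Poisson model.
- **Sensitivity:** keep the current unstratified Cox model, labelled as such, and update the Table 8 footnote.
- **SAP 4.9.2 and 4.9.3:** name the insulin covariate as use of insulin during the index pregnancy, the randomisation stratum.

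The cost is a few sentences in the SAP. No new data are needed, because the eligibility OGTT supplies the variable, and no power is lost if the two groups turn out to have equal rates.
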